#### Primary outcome measures

2.5.1

WC will be used as the primary outcome measure. This index will be assessed on week 0, 2,4,6, 8, and 12.

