### Sample size calculation

2.7

The participants will be randomly divided into moxibustion combined with characteristic lifestyle intervention of TCM (intervention group), moxibustion combined with lifestyle intervention (intervention group), the lifestyle intervention (control group) in a 2:2:1 allocation ratio. The sample size was calculated based on the primary outcome, which is proposed to be the WC. Statistical Analysis System software (version 9.3)(SAS 9.3 Institute Inc., Cary, NC) was used to calculate the required sample size.

Based on the results of previous studies and related literature reports, sample size required for each individual hypothesis testing was estimated at the 1-sided α level 0.025. With other assumptions, the basis of estimated sample sizes was listed in Table 2. To ensure adequate power for each individual hypothesis testing, a sample size of 135 was required, which consists of 54 subjects in the moxibustion combined with characteristic lifestyle intervention of TCM (intervention group), 54 subjects in the moxibustion combined with lifestyle intervention (intervention group), and 27 subjects in the lifestyle intervention (control group). Anticipating a 10% dropout rate, a total of 150 participants were recruited.

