### Statistical analysis

2.10

The SPSS software v19.0 will be used for statistical processing. The data of all participants will be conducted in the final statistical analysis which will be in accordance with the per-protocol principle and the intent-to-treat principle. Measurement data will be presented in the form of mean ± standard deviation, whereas count data will be expressed as percentage and number.

The homogeneity test of variance and normal distribution test will be adopted for measurement data. Count data and grade data will be described by rate and composition ratio. Student *t* test will be used when the data obey the normal distribution, whereas the data not obeying the normal distribution will use rank sum test. Comparison is performed by *χ*^2^ test, repeated measurement data are expressed by mean ± standard deviation and intra-group comparison is performed by analysis of variance of repeated measurement data, and inter-group comparison is by multivariate analysis of variance (MANOVA). All statistical tests will be performed on both sides, and the difference will be considered statistically significant when *P* < 0.05.

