As one of the most important traditional medical techniques in China, moxibustion has certain advantages in treating metabolic disorders. In this study, characteristic lifestyle intervention of TCM is comprised of xiusheng decoction, traditional exercises, and modern lifestyle intervention which have been commonly used in the treatment of abdominal obesity; all of them have gradually become the research hotspots in recent years. Li et al conducted a randomized controlled trial in 2018, which recruited 60 obesity patients with phlegm dampness stagnation syndrome and showed that warming needle moxibustion had positive effects on controlling clinical symptoms in these patients.^[33]^ Another randomized control trial in 2012 used a combination treatment of acupuncture and moxibustion in obesity patients at a frequency of 3 times per week for 12 weeks and found that there was significant difference in results between the control group and the treatment group.^[34]^ The study concluded that significant effects were observed since the symptoms improved after the intervention of acupuncture and moxibustion in the treatment group.^[34]^ Collectively, these effects could be the underlying impact mechanism of moxibustion on obesity. This hypothesis will be further validated in our study by the fact that moxibustion with characteristic lifestyle intervention of TCM was more effective than either moxibustion plus lifestyle intervention or lifestyle intervention alone in addressing the symptoms of abdominal obesity.

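### The between-arm test named for repeated waist circumference, MANOVA, does not test the directional pairwise comparisons that the article states and sized

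*Protocol article*

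**What the plan says.** Primary outcome measures makes WC the primary outcome: "This index will be assessed on week 0, 2,4,6, 8, and 12". It is therefore repeated measurement data.

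Statistical analysis gives such data their own rule. Within arms, "intra-group comparison is performed by analysis of variance of repeated measurement data"; between arms, "inter-group comparison is by multivariate analysis of variance (MANOVA"). All tests are two-sided at P < 0.05. No pair of arms, visit or direction is attached to the MANOVA. The same section also says "Student *t* test will be used when the data obey the normal distribution", with a rank sum test otherwise, but does not tie either test to WC, to a visit or to a pair of arms.

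The Discussion expects the trial to show that moxibustion with the TCM lifestyle package (group C) "was more effective than either moxibustion plus lifestyle intervention or lifestyle intervention alone in addressing the symptoms of abdominal obesity". Sample size calculation says that the "sample size required for each individual hypothesis testing was estimated at the 1-sided α level 0.025", and arrives at 54, 54 and 27 evaluable participants in C, B and A.

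**The concern.** The question is pairwise and has a direction: is C better than B, and is C better than A? Group B is the arm that shows what the TCM package adds to moxibustion plus ordinary lifestyle advice, so C versus B matters most.

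The null of a one-way MANOVA on the six WC values is that the vector of visit means is the same in every arm compared. A change over time that all arms share does not violate it. Any difference between arms, at any visit and in either direction, does. If moxibustion works and the TCM package adds nothing (B = C, both better than A), the claim that C beats B is false, yet the three-arm MANOVA null is false too and a small P value is expected.

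Two things are at stake. A significant MANOVA cannot by itself support the claim about C. And the power secured for each individual hypothesis belongs to a different test from the one named for the analysis.

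**Working it through.** **The plan's own figure.** 135 / (1 − 0.10) = 150. Split 2:2:1, 135 gives 54/54/27 and 150 gives 60/60/30, as stated. The 135 itself cannot be re-derived, because the inputs are in Table 2, which is not shown.

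**What 54/54/27 can detect**, at 1-sided 0.025 and 80% power, using d = (1.960 + 0.842) × √(1/n₁ + 1/n₂):
- C versus B: 2.802 × √(1/54 + 1/54) = 0.54 SD.
- C (or B) versus A: 2.802 × √(1/54 + 1/27) = 0.66 SD.

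These motivate the assumed effects below (0.55 and 0.67 SD of the week 0 to 8 change).

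**Dimension of each test.** MANOVA numerator degrees of freedom = visits × (arms − 1). Three arms: 6 × 2 = 12. Two arms: 6 × 1 = 6. The sized comparison has one, with a sign.

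**Simulation.** Arms of 27/54/54, six visits, 2,000 trials per case. Assumptions, none of them from the article: the effect builds linearly to week 8 and holds at week 12; the correlation between visits is compound-symmetric (CS) 0.70, CS 0.85, or serially decaying at 0.85 per 8 weeks. The comparator is a t test of the week 0 to 8 change, rejecting only in favour of C at 1-sided 0.025. With all arms equal, MANOVA rejects in 4.6-5.9% and the directional t tests in 2.0-3.0%, so each has about the right size for its own null.

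| Case | Test | CS 0.70 | CS 0.85 | Serial |
|---|---|---|---|---|
| C = B, both better than A by 0.67 SD of change | three-arm MANOVA | 81% | 75% | 51% |
| same | directional C-B t test | 2.6% | 2.5% | 2.5% |
| C better than A = B by 0.55 SD of change | pairwise C-B MANOVA | 85% | 80% | 56% |
| same | directional C-B t test | 79% | 82% | 81% |

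A repeat of the first case gave 82%, 78% and 51% for the three-arm MANOVA and about 3% for the directional contrast.

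**Separate check with other correlations** (CS or first-order autoregressive, 0.5 or 0.8 between adjacent visits; effects here in SD of a single WC measurement, so not on the same scale as the table):
- C = B, both 0.67 SD better than A: three-arm MANOVA rejects in 60% to 99.9%; over effects of 0.5 to 0.8 SD the range is 33% to 100%. Requiring C to beat both B and A by directional contrasts gives a false claim in about 2-3%.
- C = B at every visit: pairwise C-B MANOVA rejects in about 5%.
- C worse than B by 0.3 SD, both better than A (CS 0.8): pairwise C-B MANOVA rejects in 65%, three-arm MANOVA in about 100%, the directional C-B contrast in 0%.
- C and B equal at weeks 8 and 12, B merely falling faster before that (CS 0.8): pairwise C-B MANOVA rejects in 51%.

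**The case against.** The strongest reply is that the article does not say whether MANOVA is three-arm or pairwise, nor that a claim for C over B would rest on its P value alone. An omnibus test followed by pairwise comparisons is ordinary practice. The named t test and the reference to individual hypotheses both hint at it, and follow-up contrasts are commonly left to an SAP. This stands as a limit on the size of the problem. A reader might infer from the table that the planned analysis would wrongly declare C superior to B in 50-80% of trials. The documents do not support that: the rates apply only to a three-arm test read with no follow-up.

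On the pairwise reading the harm is smaller. Error is about 5% when C and B are equal throughout, and power is not lost under compound symmetry. A reader might also infer that MANOVA leaves the trial underpowered in general, or that including week 0 is what costs power. Neither is shown; the loss appears in one of the three correlation structures tried. Any two-sided test can also reject when C is worse, and the means then show the direction.

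Finally, the hypothesis is a Discussion sentence about symptoms, not a formal hypothesis on WC. That is fair. But Sample size calculation independently bases the sizing on WC and on individual 1-sided tests, so the mismatch does not depend on that sentence.

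What remains is that MANOVA is the only test the article ties to between-arm comparison of repeated data. The generic t test is not assigned to WC or to any pair of arms. This is a named test that does not fit the stated question, not a detail left out.

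**Conclusion.** The concern holds in a limited form. The between-arm test fixed for the primary outcome is non-directional, has no target visit and, with three arms, does not identify the pair that differs. It matches neither the comparisons the article states nor those it sized at 1-sided 0.025.

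The size depends on the reading. As a three-arm test without follow-up, it would be significant in roughly 50-80% of trials when C adds nothing over B and both beat A by about 0.67 SD of change, against about 2.5-3% for a directional C-B contrast. Pair by pair, error is sound when C and B are equal at every visit, and about 25 points of power (56% against 81%) can be lost if correlation decays over time. All percentages rest on assumed effects, time course and correlations, because Table 2 is not shown. The mismatch between test and claim does not depend on them.

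It would go too far to say that the documents require C to beat both comparators, or that they make week 8 the primary visit. They state neither.

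**What to change.** In section 2.10, replace MANOVA as the test supporting efficacy claims on WC with the pairwise contrasts C minus B, C minus A and B minus A in change in WC from week 0 to one prespecified visit. Report each with a 95% CI and test it at two-sided 0.05. For a claim in favour of C this equals the 1-sided 0.025 used for sizing, so it also reconciles sections 2.7 and 2.10.

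State which contrast supports which claim: C over B rests on C minus B, C over A rests on C minus A, and a claim that C beats both needs both. The sponsor chooses the visit; week 8, the end of treatment, is one option. MANOVA may stay as a supportive analysis.

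The cost is wording only, with no new data or participants. The downside is that a claim over both comparators is stricter than one omnibus P value. Under the simulation assumptions the chance of meeting both contrasts is 80-82% if each step from A to B to C is 0.55 SD of change. It is 54-57% if B equals A and C is 0.55 SD better, because arm A is small.

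### The plan promises intent-to-treat on everyone but compares arms on repeated data by MANOVA, which as normally run keeps only participants with every visit

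*Protocol article*

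**What the plan says.** All references are to the protocol article.

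- **Who is analysed.** Statistical analysis (2.10): "The data of all participants will be conducted in the final statistical analysis which will be in accordance with the per-protocol principle and the intent-to-treat". Both sets are named, and neither is called primary.
- **How repeated data are compared.** The same section gives one method within groups, "intra-group comparison is performed by analysis of variance of repeated measurement data", and another between groups: "inter-group comparison is by multivariate analysis of variance (MANOVA". It also lists the t test and the rank sum test for measurement data in general.
- **What is repeated.** Primary outcome measures (2.5.1), on WC: "This index will be assessed on week 0, 2,4,6, 8, and 12". That is one baseline and five post-baseline values.
- **Expected loss.** Sample size calculation (2.7): "To ensure adequate power for each individual hypothesis testing, a sample size of 135 was required", and then "Anticipating a 10% dropout rate, a total of 150 participants were recruited".

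**The concern.** Two statements in one section pull against each other. The first promises that everyone is analysed under intent-to-treat. The second assigns between-group comparison of repeated data to a method that needs a full set of visits from each person. The plan itself expects one participant in ten to leave, so the named method cannot, as normally run, analyse the promised population.

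What is at stake is the comparability that randomisation provides. Completing all visits is a selection made after randomisation. Two arms attend 48 moxibustion sessions over 8 weeks and the control arm attends none. The arm with the TCM lifestyle package adds a decoction and daily exercise on top of moxibustion. The Introduction itself says adherence to diet and activity interventions is poor. People may therefore leave the three arms for different reasons, and a contrast among completers can be biased by that. It also discards WC values that dropouts provided before they left.

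**Working it through.** **Inputs from the protocol article:** 135 evaluable participants (54 + 54 + 27), 10% dropout, 150 recruited (60 + 60 + 30), five post-baseline WC visits, one-sided α of 0.025 for sample size.

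**Inputs assumed here:** a miss rate *m* per post-baseline visit among participants who stay, independent across visits, and planned power of 80% or 90%. The power and effect size are in Table 2, which is not shown, so the 135 itself cannot be rebuilt.

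**Step 1. The plan's own figure.** 135 / (1 − 0.10) = 150. By arm, 54 / 0.9 = 60 and 27 / 0.9 = 30. The inflation reproduces exactly.

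**Step 2. Dropout alone.** Complete cases = 150 × 0.90 = 135, so 150 − 135 = 15 randomised participants are left out. This is not a shortfall against the required number.

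**Step 3. What is discarded.** One data set was simulated with 150 participants, of whom 15 dropped out at random visits. A MANOVA on the five post-baseline values used 135 rows. The 15 dropouts had 45 observed WC values, 15 of them baseline, so 45 − 15 = 30 observed post-baseline values were thrown away. In that data set 148 of 150 participants had at least one post-baseline WC and could have contributed to a mixed model. The 45 and the 148 depend on the simulated dropout times; the 15 lost participants do not.

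**Step 4. Dropout plus missed visits.** Complete cases = 150 × 0.90 × (1 − *m*)^5.

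**Step 5. Power for a pairwise contrast of means.** For 54 v 27, the standardised difference that gives 80% power is (1.960 + 0.842) × √(1/54 + 1/27) = 0.660. For 90% it is (1.960 + 1.282) × √(1/54 + 1/27) = 0.764. If all arms shrink by the same factor *f* = (1 − *m*)^5, power becomes Φ[(1.960 + z) × √f − 1.960], with z = 0.842 or 1.282. The arm sizes cancel, so the result also holds for 54 v 54.

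| *m* per visit | Complete cases | Power if planned at 80% | Power if planned at 90% |
|---|---|---|---|
| 0% | 135 | 80% | 90% |
| 1% | 128 | 78% | 89% |
| 2% | 122 | 76% | 87% |
| 3% | 116 | 74% | 85% |
| 5% | 104 | 69% | 81% |

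Worked line for *m* = 5%: f = 0.95^5 = 0.774, and 135 × 0.774 = 104. With planned 80%, Φ(2.802 × 0.880 − 1.960) = Φ(0.504) = 69%.

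These powers are for a two-arm comparison of means, not for the MANOVA test. They show what the loss of participants does to the contrasts that the sample size section says it powers.

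**The case against.** **Imputation is not ruled out.** A reader might infer that intent-to-treat will definitely not be delivered. The article does not support that. It is silent on missing data, and a missing-data rule is commonly left to the full protocol or analysis plan. If values are filled in first, MANOVA can include every randomised participant. This objection stands, and it makes the point conditional.

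**The analysis sets are unranked, not declared equal.** A reader might take the joint mention of per-protocol and intent-to-treat as giving them the same standing. The text assigns no rank, and choosing the primary set is ordinary analysis-plan content. Leaving it open is not an error in itself. Naming the primary set is worthwhile only because the sentence is being rewritten anyway.

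**MANOVA is not tied to WC by name.** This is correct. The link is an inference, but a strong one, since WC is the primary outcome, is measured repeatedly, and the section sends repeated data to this method.

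**MANOVA can speak to single visits.** A reader might say it returns only one overall P value. It is routinely accompanied by univariate tests for each visit, and the listed t test could also give a visit-level contrast. The point therefore does not rest on this.

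**The power loss is not in the documents.** A reader might infer that the planned dropout already leaves the trial underpowered. It does not: 10% dropout leaves exactly 135. Any loss below that needs missed visits among stayers, for which the article gives no rate.

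**The bias has no known size or direction.** This is also true, and the contrast between the two moxibustion arms is less exposed because both attend the same sessions. The added decoction and exercise still separate those arms, so the risk is smaller there but not absent.

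**Conclusion.** The point holds in a limited form. The article pairs a promise to analyse everyone with a method that, as normally run, keeps only complete cases. At the plan's own dropout rate this sets aside about 15 of 150 randomised participants (10%) and the WC values already collected from them. The conclusion rests on two conditions: that MANOVA is applied to WC, and that no imputation comes first.

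The main consequence is possible selection bias and lost information, of unknown direction and size. Loss of power is secondary and depends wholly on assumptions: 1% to 5% missed per visit, independent across visits, and a planned power of 80% or 90%. The documents do not support saying that the trial falls short of 135 through planned dropout, or that intent-to-treat has been abandoned. The change is worth making because a better method is available at very little cost.

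**What to change.** In Statistical analysis, replace MANOVA for WC with a likelihood-based mixed model for repeated measures. The terms are arm, week, arm × week and baseline WC, with an unstructured covariance over the post-baseline visits. It should use every available visit of every randomised participant, by assigned arm. Read the pairwise arm contrasts from it at one prespecified week. State that this intent-to-treat analysis is primary and that per-protocol is a sensitivity analysis. If MANOVA is kept instead, state the imputation that precedes it and the contrasts to be reported.

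The cost is a few sentences, with no extra participants or visits. The SPSS version already named can fit the model with its MIXED procedure. The downside is that the model relies on missing-at-random, so one sensitivity analysis that departs from that assumption should be added. The model also gains no outcome information from anyone who has no post-baseline WC.

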## Discussion

3

The prevalence of overweight and obesity in 18 years or older population is about 72.5% in Mexico, whereas the prevalence of abdominal obesity almost reaches 76.6%, according to the Half Way National Survey of Health and Nutrition (ENSANUT MC) 2016, and this frequency is expected to increase.^[26]^ Abdominal obesity has been closely linked to insulin resistance, inflammation, full-blown diabetes, or blood lipid disorders, and even an increased risk of developing metabolic syndrome, cardiovascular disease, Alzheimer disease.^[27–29]^ Abdominal obesity has been considered to be the most influential cause of chronic liver disease which is associated with non-alcoholic fatty liver disease.^[30]^ Both abdominal obesity and general obesity have been regarded as the major public health concerns in the world. Also, a large economic burden caused by obesity has been imposed on the individual, families, and even nations.^[31]^ The global economic impact of obesity was estimated to be US $2.0 trillion or 2.8% of the global gross domestic product in 2014.^[32]^ Therefore, it is important to discover cost-effective therapy for obesity, especially abdominal obesity.

During the past 40 years, it has been illustrated that abdominal obesity is mainly caused by a dysfunction between the kidney, spleen, and the triple energizer in Chinese medicine research, and its pathogenesis is closely associated with many dysfunctional mechanisms of these visceral organs, with the involvement of stagnation of phlegm. We designed this study to examine the safety and efficacy of moxibustion combined with characteristic lifestyle intervention of TCM in the treatment of abdominal obesity. The patient's obesity-related indicators, serum biochemical indexs, blood pressure, conversion score of physical symptoms, and measurement of the scale will be recorded and reported.

As one of the most important traditional medical techniques in China, moxibustion has certain advantages in treating metabolic disorders. In this study, characteristic lifestyle intervention of TCM is comprised of xiusheng decoction, traditional exercises, and modern lifestyle intervention which have been commonly used in the treatment of abdominal obesity; all of them have gradually become the research hotspots in recent years. Li et al conducted a randomized controlled trial in 2018, which recruited 60 obesity patients with phlegm dampness stagnation syndrome and showed that warming needle moxibustion had positive effects on controlling clinical symptoms in these patients.^[33]^ Another randomized control trial in 2012 used a combination treatment of acupuncture and moxibustion in obesity patients at a frequency of 3 times per week for 12 weeks and found that there was significant difference in results between the control group and the treatment group.^[34]^ The study concluded that significant effects were observed since the symptoms improved after the intervention of acupuncture and moxibustion in the treatment group.^[34]^ Collectively, these effects could be the underlying impact mechanism of moxibustion on obesity. This hypothesis will be further validated in our study by the fact that moxibustion with characteristic lifestyle intervention of TCM was more effective than either moxibustion plus lifestyle intervention or lifestyle intervention alone in addressing the symptoms of abdominal obesity.

Among many of the mechanisms of abdominal obesity, chronic inflammation, cell apoptosis, energy imbalance, and gut microbial enterotypes can result in an excessive accumulation of adipose tissue.^[35,36]^ It is possible that moxibustion treatments could lead to the inhibition of inflammatory, promotion of energy metabolism, and reduction of pro-inflammatory cytokines. It has been shown that the clinical effects of moxibustion may encompass neural modulation, anti-inflammatory, immunity enhancement, and acceleration effects of the metabolism.^[37]^ A number of studies showed that moxibustion had some positive effects on the obesity-related parameter in abdominal obesity patients; however, insufficient evidence on moxibustion temperature, and treatment duration made results difficult to interpret. In addition, lifestyle changes (exercise, diet control) can reduce anthropometric indexes in patients with abdominal obesity and these interventions are focused on improving fat consumption and metabolism capacity.^[38]^ Also, moxibustion and lifestyle changes have many other advantages, including low-cost, stable efficacy, and low risks of complications. Although some studies confirmed such beneficial effects of moxibustion or lifestyle changes in improving abdominal obesity symptoms, the combined effects of moxibustion, and characteristic lifestyle intervention of TCM which includes lifestyle changes on abdominal obesity still remains unclear.

In this study protocol, we will use moxibustion at 4 acupoints for the treatment period of 8 weeks combined with characteristic lifestyle intervention of TCM for 12 weeks which also includes the follow-up period of 4 weeks. The outcome evaluations will include analyses of obesity-related indicators, serum biochemical indexs, blood pressure, conversion score of physical symptoms, and measurement of the scale. Besides, some limitations still exist in this proposed study. First, the effects of one 8-week treatment session will be observed and the effects of 4 time points will be mainly focused on during the intervention period. Because our purpose in this study is mainly to evaluate the safety of the major treatment and longer-term effects on improving obesity-related clinical symptoms, a relatively long treatment period will be required to determine the longer-term effect of this combined therapy and whether it is acceptable and safe for patients to use frequently. Secondly, the sample size is not enough and the blinding method cannot be completely used for the moxibustion therapist which will result in a bias risk of this clinical trial to some extent. Nevertheless, we expect that this study will be able to provide some new evidence regarding the combined effect of moxibustion and characteristic lifestyle intervention of TCM in the treatment of abdominal obesity.

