Moxibustion, arose from TCM, has been widely applied in clinical practice. A number of studies have demonstrated that moxibustion is effective in enhancing the immune system, and modifying neurotransmitter levels of central nervous system through repeated acupoint stimulation.^[16,17]^ Studies have shown that moxibustion induces a smoother flow of qi and blood in the human body by using moxa to warm acupoints and body regions, accelerates the blood circulation overall, thereby achieving the effects of disease prevention and health care.^[18]^ Moxibustion can be applied to patients indirectly (placing a medium between the skin and the burning moxa) or directly (placing burn cones directly onto the skin). Moxibustion may be a good choice with patients and doctors for its unique advantages of effectiveness, convenience, and simplicity.

Thus far, moxibustion interventions have been studied in both clinical trials and animal models. Several studies in animal models have shown the positive effects of moxibustion in prevention and treatment of endocrine issues and excess body weight. For example, some researches have proved that moxibustion had beneficial effects on blood lipids, fat accumulation, and decrease of adrenocorticotrophic hormone which plays a key role in decreasing blood flow into fat tissue in rats.^[19,20]^ In one previous clinical trial, Mestre et al found that obesity index decreased and the rate of body weight gain was slowed after the moxibustion treatment.^[21]^ Another study conducted by Huang et al^[22]^ showed that moxibustion was effective in reducing blood lipid indexes and the levels of Leptin, Resistin for the patients with obesity complicated with hyperlipidemia. All of these results suggest that moxibustion has beneficial effects on both body weight management and blood lipids.

To evaluate the exact effect of moxibustion on the clinical efficacy of abdominal obesity, we will conduct a 3three-arm parallel clinical trial. In this study, we will try to combine the advantages of moxibustion and characteristic lifestyle intervention of TCM in the treatment of abdominal obesity. To achieve this, a standardized multicenter, randomized, controlled trial will be carried out to improve the treatment protocol and evaluation criteria, which can provide an objective theoretical basis and methodology for the treatment of abdominal obesity by moxibustion combined with characteristic lifestyle intervention of TCM.

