##### Lifestyle intervention

2.4.2.2

The lifestyle intervention in this group will be the same as that for the group A.

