##### Moxibustion

2.4.3.1

The specific methods and intervention time in this group will be the same as that for the group B.

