##### Characteristic lifestyle intervention of TCM

2.4.3.2

In this study, xiusheng decoction, traditional exercises, and modern lifestyle intervention will be combined as the characteristic lifestyle intervention method of TCM to help participants establish healthy living habits.

(1)Xiusheng DecoctionThe package (specification: 6 g) manufactured by hubei ji’antang pharmaceutical Co., Ltd. is adopted, the manufacturer conforms to GMP standard with strict quality control. The components of this product are all Chinese medicines with medicinal and food homologous (composition: coix seed, black tea, tuckahoe, lotus leaf, xylitol, dextrin), and the dosage form is granule. Each decoction should be taken twice a day, orally half an hour after meals. The treatment will be delayed during the menstrual period. The course of intervention will last for 8 weeks.(2)Traditional exercisesIt is recommended that the “fitness qigong • ba duan jin” issued by the fitness qigong management center of general administration of sport of China be taken as the standard for performing meritorious exercises. A full set of fitness qigong consists of 8 forms in which the essentials of these movements refer to “Chinese Traditional Health sports and Health Preservation,” and the movements will be instructed by the extension agents of traditional sports who have been trained by Shanghai qigong research institute. The exercise will be taken for 35∼40 minutes every day, 7 times a week. The intervention will be conducted for 8 weeks.(3)Modern lifestyle interventionThe lifestyle intervention in this group will be the same as that for the group A.

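### The Discussion rests a hypothesis about moxibustion on group C beating groups B and A, but only B versus A isolates moxibustion

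*Protocol article*

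**What the plan says.** The Introduction (section 1) opens its statement of purpose with "To evaluate the exact effect of moxibustion on the clinical efficacy of abdominal obesity" and then turns to the combination of moxibustion with the TCM lifestyle programme.

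The Discussion (section 3) summarises two earlier trials that used moxibustion and concludes: "Collectively, these effects could be the underlying impact mechanism of moxibustion on obesity". The next sentence reads "This hypothesis will be further validated in our study by the fact that moxibustion with characteristic lifestyle intervention of TCM was more effective" and continues "than either moxibustion plus lifestyle intervention or lifestyle intervention alone in addressing the symptoms of abdominal obesity". The comparisons named are therefore C with B and C with A. B with A is not named there.

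The arms are defined in section 2.4:
- Group A receives the lifestyle intervention (2.4.1).
- Group B receives moxibustion plus lifestyle. On the lifestyle part, 2.4.2.2 says: "The lifestyle intervention in this group will be the same as that for the group A".
- Group C receives moxibustion plus the TCM lifestyle programme. On moxibustion, 2.4.3.1 says: "The specific methods and intervention time in this group will be the same as that for the group B". On the programme, 2.4.3.2 says that "xiusheng decoction, traditional exercises, and modern lifestyle intervention will be combined as the characteristic lifestyle intervention method of TCM", and its modern lifestyle part is again that of group A. The qigong lasts 35-40 "minutes every day, 7 times a week. The intervention will be conducted for 8 weeks".

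**The concern.** The hypothesis concerns moxibustion, but the evidence offered for it comes from two comparisons that do not isolate moxibustion. In one, moxibustion is the same on both sides. In the other, it changes together with an oral preparation and a daily exercise programme.

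The risk is a wrong conclusion in either direction. If the decoction or the qigong reduces waist circumference and moxibustion does not, group C can beat both other groups, and a report that follows this sentence would credit moxibustion. If moxibustion works and the additions do nothing, C will resemble B, and the same sentence would withhold support from a treatment that works. The first risk is plausible on the protocol's own account, because the Discussion says that exercise and diet changes reduce anthropometric indexes, and the primary outcome is one of these.

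**Working it through.** **What each contrast contains.** Let L be the lifestyle intervention, M the addition of moxibustion to it, and X the addition of decoction and qigong to both. From sections 2.4.1 to 2.4.3:

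- A = L
- B = L + M
- C = L + M + X

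Hence:

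- C − B = X. Moxibustion cancels.
- C − A = M + X. Moxibustion is confounded with the additions.
- B − A = M. Moxibustion added to lifestyle, alone.

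This does not need additive effects, since X can be read as the effect of decoction and qigong given moxibustion. Nor does meeting both named comparisons help: with M = 0 and X > 0, both C − B and C − A are positive. With M > 0 and X = 0, C − B is zero. There is no sham arm, so M includes any non-specific effect of receiving moxibustion sessions.

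**Sample size.** Section 2.7 gives 54, 54 and 27 evaluable (135) and 10% dropout. 135 / 0.9 = 150, 54 / 0.9 = 60 and 27 / 0.9 = 30, which reproduces the stated 150. The 135 itself cannot be checked, because its assumptions are in Table 2, which is not shown.

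**Illustration with assumed effects.** The documents shown give no effect sizes, so those below are assumptions in SD units. Simulation: 40,000 trials per scenario, groups of 27 (A), 54 (B) and 54 (C), SD 1, t tests at two-sided 0.05.

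| Assumed M | Assumed X | C better than both B and A | B better than A |
|---|---|---|---|
| 0 | 0.5 | 46% | 2.5% |
| 0 | 0.7 | 81% | 2.5% |
| 0 | 0.9 | 96% | 2.3% |
| 0.7 | 0 | 2.4% | 83% |

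The first three rows show the pattern named in the Discussion appearing often when moxibustion does nothing. The last shows it almost never appearing when only moxibustion works.

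**Extra exercise prescribed in group C.** Inputs: 35-40 minutes on 7 days (2.4.3.2); activity of at least 210 minutes a week, preferably at least 270 (2.4.1).

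- 35 × 7 = 245 and 40 × 7 = 280 minutes a week.
- Against the minimum: 245 / 210 = 1.17 and 280 / 210 = 1.33, so 117-133%.
- Against the preferred level: 245 / 270 = 0.91 and 280 / 270 = 1.04, so 91-104%.

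These ratios describe added exercise only if qigong comes on top of the weekly target. Section 2.4.3.2 lists it as a separate component but does not say whether its minutes may count towards the target.

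**Precision of the isolating contrast.** With 54 against 27, the detectable difference for B versus A is (1.960 + 0.842) × √(1/54 + 1/27) = 0.66 SD at an assumed 80% power, or 0.76 SD at 90%. For C versus B, with 54 against 54, the figures are 0.54 and 0.62 SD.

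**The case against.** The best defence is that the trial is mainly about the combination. The abstract and most of the Discussion give that as the objective, and the Introduction moves to it straight after naming moxibustion. For that aim C versus A is the right contrast for the whole package, and C versus B is right for what the TCM additions contribute. This stands, and it limits the point to conclusions about moxibustion. It does not remove the point: the sentence immediately before the claim is about moxibustion alone, and the Introduction states moxibustion's own effect as an aim.

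A reader might also infer more than the documents support:

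- **That the trial has a formal rule for declaring moxibustion validated.** It does not. The sentence is narrative in the Discussion. Section 2.7 refers only to individual hypothesis tests, and section 2.10 sets no success criterion. The simulated percentages therefore illustrate the reasoning and are not error rates of a planned test.
- **That B versus A is missing from the trial's hypotheses.** This cannot be known. Table 2, which gives the sample size for each hypothesis, is not shown and may include it. Its presence there would not correct the Discussion sentence, but the omission would then be confined to that sentence.
- **That C must beat B and A in a joint test, with a loss of power, or that synergy is claimed.** No section requires a joint test, and the text speaks of combined effects, not of interaction.

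**Conclusion.** The point holds as one of inference. Neither contrast named in the Discussion, nor the two together, can show an effect of moxibustion. Only B versus A isolates moxibustion added to lifestyle, and without a sham it does so with non-specific effects included. This follows from the arm definitions and needs no numerical assumption.

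The arms themselves are sound for the questions they can answer. The defect lies in which comparison is said to support which claim. The simulation rests on assumed effects. The 245-280 minutes a week of qigong shows why group C's advantage could come from something other than moxibustion, subject to the open question of whether those minutes are additional.

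**What to change.** Replace the Discussion sentence and state which conclusion each contrast supports:

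- **B versus A:** the effect of moxibustion added to the lifestyle intervention. Any conclusion about moxibustion itself rests on this, with the absence of a sham acknowledged.
- **C versus B:** the effect of adding decoction and qigong together, not attributable to either component.
- **C versus A:** the effect of the full combined package, which is the trial's other stated aim.

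State also whether the qigong minutes are additional to the weekly activity target, so that readers can judge the contrast in exercise. If Table 2 already lists B versus A, refer to it in the revised sentence.

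The cost is wording only: no arm, visit, outcome or sample size changes. The downside is a narrower claim for C over B. The moxibustion question also rests on the smaller 54 against 27 comparison, which can detect only a larger difference than C versus B.
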